## Introduction

1

Chronic obstructive pulmonary disease (COPD) is a chronic inflammatory disorder caused by the inhalation of tobacco smoke or other irritants. It is characterized by progressive deterioration in pulmonary function and persistent airway inflammation. Its symptoms include difficulty in breathing, coughing, mucus (sputum) production, and wheezing.^[1]^ Patients with COPD usually exhibit an upper chest breathing pattern and dyspnea on exertion. The disease also presents extrapulmonary manifestations such as skeletal muscle dysfunction, which is an important prognostic factor that justifies exercise intolerance in these patients.^[2]^

Several treatment strategies for COPD are provided in the current literature, which includes limited bed rest, pharmacological therapy, Oxygen therapy, and physiotherapy. Physiotherapy interventions, such as breathing exercises and early mobilization, aim to restore or maintain muscle function during an acute episode of COPD.^[3–5]^ Physical therapists often use these strategies to relieve dyspnea, improve thoracoabdominal coordination, and enhance functional capacity in patients with COPD exacerbations.^[6]^

A relatively new treatment method for COPD is kinesio taping (KT), which is being widely used as a relatively novel band-aid method to reduce the pain of musculoskeletal disorders. KT is an elastic bonding material containing high tensile capacity, which ensures the free movement of the application area without the need of drugs or chemicals. KT can be extended to 140% of the original length, providing a good range of motion in comparison with other types of tape.^[7,8]^ Studies have shown that KT improves blood and lymph circulation, mitigates pain, adjusts joints, and relives muscle tension. Although the effect of KT on pain is unclear, KT may provide afferent stimuli that promote pain inhibition mechanisms and pain relief.^[9,10]^ Depending on the proposed effects, we speculated that if KT were applied to thorax, it could have some beneficial effects to restore respiratory muscle function and to reduce hyperinflation, thereby resulting in increased functional capacity for patients with COPD.

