### Population

2.2

Participants recruited into the study need to fulfill the following criteria: clinical diagnosis of COPD and symptoms indicative of exacerbation; spontaneous breathing on hospital admission; and physiotherapy since the first day of hospitalization. The exclusion criteria are as follows: patients who are uncooperative, those have previous thoracic surgery, thoracic deformities or any condition that make it difficult to apply the KT, and those with reports of allergic skin reactions to the use of adhesive bandages, plasters, or other adhesive materials.

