### Outcome measure

2.5

The outcome measures are pulmonary function and respiratory muscle strength. Pulmonary function was measured using a spirometer. To perform the measurement, subjects were instructed to sit on an armless chair with back support while their knees flexed to 90° and nostrils occluded by a nose clip. Then they performed a maximal inspiration followed by a forced expiration, exhaling as much air as possible 3 seconds. This maneuver was repeated 3 times, and the highest scores were recorded for analyses. Respiratory muscle strength will be measured as maximum inspiratory pressure (MIP) and maximum expiratory pressure (MEP), using an analogic manovacuometer. The assessments are performed in accordance with American Thoracic Society/European Respiratory Society standards (2002). The participants are assessed in the seated position. The MIP maneuver begins near residual volume, and the MEP maneuver begins near total lung capacity. The maximum score of 3 maneuvers varying by less than 20% will be recorded.

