### Statistical analysis

2.6

All analyses will be performed using SPSS for Windows, version 16, and GraphPad InStat. Analysis of variance is used for comparing mean values of patient's age, weight, height, and body mass index. For nonparametric measures, differences between baseline and posttreatment scores for each group are computed by the Wilcoxon signed ranks test. The difference between each treatment group is performed by the Kruskal–Wallis test. The level of statistical significance is set as *P* < .05.

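### The spirometry instruction gives 3 seconds as its only exhalation time; read as a limit, it would truncate any vital capacity or FEV1/FVC taken from these COPD patients

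*Protocol article*

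**What the plan says.** Section 2.5 (Outcome measure) of the protocol article names two outcome domains: "The outcome measures are pulmonary function and respiratory muscle strength". It does not say which spirometric variables represent the first. FVC, FEV1 and their ratio are not named anywhere in the article.

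The manoeuvre itself is set out in some detail, including the chair, the knee angle and the nose clip. The text continues: "Then they performed a maximal inspiration followed by a forced expiration", and the patient is described as "exhaling as much air as possible 3 seconds". No preposition or qualifier stands before the time, so the sentence does not say whether 3 seconds is a limit or a minimum. The value to keep is then fixed: "This maneuver was repeated 3 times, and the highest scores were recorded for analyses".

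A measurement standard is cited later in the same section: "The assessments are performed in accordance with American Thoracic Society/European Respiratory Society standards (2002"). That sentence comes after the introduction of MIP and MEP and before the details of those two tests, so it does not clearly govern the spirometry.

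Section 2.2 (Population) requires "clinical diagnosis of COPD and symptoms indicative of exacerbation".

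**The concern.** A forced expiration of as much air as the patient can manage is a vital-capacity manoeuvre. It yields vital capacity only if the patient is allowed to finish. In airflow obstruction, a material part of the volume may still be in the lung at 3 seconds, and this part grows with the severity of obstruction. If the effort ends there, the recorded quantity depends on how fast the lung empties as well as on how much it can empty.

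Two consequences follow if FVC or FEV1/FVC is taken from this manoeuvre. FVC is understated and the ratio overstated, most in the most obstructed patients. And the change from baseline to day 15 loses its plain meaning: faster emptying would appear as a larger volume, while a change in the air expelled after 3 seconds would not be seen at all. Pulmonary function is one of only two outcome domains, so its interpretation matters to what the trial can report.

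**Working it through.** The article gives no figure on this point to reproduce. The check has two parts: what the text allows, and how large the truncation would be under stated assumptions.

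**1. The text**

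- Exhalation time: 3 seconds, with no qualifier (section 2.5).
- Value kept: the highest of three efforts (section 2.5). This does not repair a time limit, because all three efforts would share it.
- Cited standard: placed within the MIP and MEP text (section 2.5), so it cannot be relied on to override the spirometry wording.
- Population: COPD with symptoms of exacerbation (section 2.2). No baseline FEV1/FVC is given, so the ratios below are assumptions.

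**2. Size if 3 seconds is a limit: single-exponential emptying (assumption)**

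Let q be the true FEV1/FVC. The fraction of FVC expired by time t is 1 − (1 − q)^t. At t = 3 it is 1 − (1 − q)³, and the apparent ratio is q divided by that fraction.

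| True q | 3-second volume / FVC | Apparent ratio |
|---|---|---|
| 0.7 | 1 − 0.3³ = 0.973 | 0.7 / 0.973 = 0.719 |
| 0.6 | 1 − 0.4³ = 0.936 | 0.6 / 0.936 = 0.641 |
| 0.5 | 1 − 0.5³ = 0.875 | 0.5 / 0.875 = 0.571 |
| 0.4 | 1 − 0.6³ = 0.784 | 0.4 / 0.784 = 0.510 |
| 0.3 | 1 − 0.7³ = 0.657 | 0.3 / 0.657 = 0.457 |

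Over this range FVC is understated by about 3% to 34%, and the ratio is overstated by about 0.02 to 0.16.

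**3. Sensitivity to the model: two compartments (assumption)**

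V(t) = s(1 − e^(−t/0.5)) + (1 − s)(1 − e^(−t/τ)), with fast share s = 0.3 or 0.5 and slow time constant τ = 2, 3 or 5 seconds. FVC is taken at 15 seconds.

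| s | τ (s) | True ratio | 3-second volume / FVC | Apparent ratio |
|---|---|---|---|---|
| 0.3 | 2 | 0.535 | 0.843 | 0.634 |
| 0.3 | 3 | 0.460 | 0.745 | 0.617 |
| 0.3 | 5 | 0.400 | 0.637 | 0.628 |
| 0.5 | 2 | 0.629 | 0.887 | 0.709 |
| 0.5 | 3 | 0.576 | 0.818 | 0.705 |
| 0.5 | 5 | 0.536 | 0.743 | 0.722 |

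FVC is understated by 11% to 36%, and the ratio is overstated by about 0.08 to 0.23. The single-exponential figures are therefore not an extreme case. For s = 0.3, the true ratio falls from 0.535 to 0.400 while the apparent ratio stays between 0.617 and 0.634, so the truncated ratio barely separates these patients.

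**4. What this does to a change score**

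Suppose the true ratio moves from 0.40 to 0.50 with FVC unchanged. Under the single-exponential model the 3-second volume rises by 0.875 / 0.784 = 1.116, about 12%, although no volume was gained. This case implies a true FEV1 rise of 0.50 / 0.40 = 1.25, or 25%. It shows the mechanism and is not a forecast. In the other direction, at a true ratio of 0.40, 1 − 0.784 = 21.6% of FVC is expired after 3 seconds, and any change confined to that part goes unrecorded.

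**The case against.** The strongest reply is that the finding hangs on a broken phrase. If the missing words mean a minimum of 3 seconds, the instruction truncates nothing. That stands: truncation is the likelier reading, not an established fact. The sentence would still need correcting, because two assessors could apply it differently.

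Second, the article never names FVC or FEV1/FVC. A trial that reported only FEV1 would not be touched. This also stands, and the harm is conditional on those variables being taken from this manoeuvre.

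Third, a condensed article commonly leaves end-of-test and acceptability rules to the full protocol. Agreed: their absence is not the point here. The point is a manoeuvre time that the article does state, and states badly.

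Three stronger conclusions are tempting and are not supported.

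- A reader might infer that the treatment comparison is biased. Section 2.5 describes one manoeuvre for everyone, with no difference by arm or visit, so the limit does not by itself create a difference between randomised groups. If taping changed emptying speed in one arm, that would be a real effect on pulmonary function, but mislabelled as volume.
- A reader might infer that a stated aim of reducing hyperinflation is undermined. Hyperinflation appears only in the Introduction, as a speculated mechanism. The stated purpose is respiratory function and muscle strength.
- A reader might take the 12% as an expected error. It comes from a constructed case in which FEV1 truly rises by 25%, and nothing in the article suggests a shift of that size.

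**Conclusion.** The point holds in conditional form. Section 2.5 gives 3 seconds as the only exhalation time and leaves its meaning open. If it is a limit, any vital capacity or FEV1/FVC from this manoeuvre is truncated. The loss in FVC is about 6% at a true ratio of 0.6 and about 34% at 0.3 under single-exponential emptying, and 11% to 36% under the two-compartment variants tried.

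These sizes rest on assumed emptying models and assumed ratios, because the article gives no baseline spirometry. The direction, and the growth with severity, do not depend on the exact model. FEV1, MIP and MEP are unaffected. The damage is to the validity and interpretation of volume-based results, not by itself to the fairness of the comparison between arms. It is worth correcting before measurement starts, because tracings that end at 3 seconds cannot be extended afterwards.

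**What to change.** In section 2.5, replace the 3-second wording with an instruction to continue the forced exhalation until the volume-time curve plateaus or the patient cannot continue. Apply it identically at baseline and day 15 in both arms, and record the exhalation time of each effort. In the same place, name the spirometric variables to be analysed.

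If 3 seconds is to be kept as a limit, say so, label the measure a 3-second forced expiratory volume, and do not report it as FVC or use it in FEV1/FVC.

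The cost is a few more seconds of effort per manoeuvre on the same spirometer. Some patients may stop early; the recorded exhalation time makes that visible at analysis.

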### Statistical analysis

2.6

All analyses will be performed using SPSS for Windows, version 16, and GraphPad InStat. Analysis of variance is used for comparing mean values of patient's age, weight, height, and body mass index. For nonparametric measures, differences between baseline and posttreatment scores for each group are computed by the Wilcoxon signed ranks test. The difference between each treatment group is performed by the Kruskal–Wallis test. The level of statistical significance is set as *P* < .05.

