### Random and blind

2.3

Before starting the study, a randomization list is produced using software-generated randomized numbers; the randomization depends on random blocks of 10. Patients will not know to which group they are assigned or which treatment they will be offered. Patients will be assigned at random to the COPD medical treatment + KT (Group 1), or the COPD medical treatment alone (Group 2). Participants are enrolled by the research assistant. After baseline examination, all patients will be given a full explanation of the treatment protocol and will be required to sign a written informed consent for study participation and for publication of the results. All the data collectors, doctors, statistical analysts, as well as result assessors are not aware of grouping assignment (Fig. 1).

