### Intervention protocol

2.4

In Group 1, KinesioTex Gold is used for KT application. Patients are seated on a chair. When the patients are at the end of the expiration, it will be applied bilaterally on the fifth to sixth and ninth to tenth intercostal muscles transversally and on the anterior and posterior axillary line longitudinally with 50% tension. To stimulate the muscle and support the function, the stimulation technique is usually applied from the origin to the insertion of the muscle with the recommended stretching of 25 to 50%. KT is changed on every fifth day (for a total of 3 times and 15 days) by the same certified physiatrist who has previously attended the KT training course. The patients are instructed not to take the tapes off at any time but they are allowed to take showers. The researcher, who is blind to the type of treatment, completes posttreatment (15th day) evaluations for each patient and recorded the data.

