## Discussion

3

The purpose of medical treatment of COPD is to reduce the frequency and severity of the symptoms and to improve the functional capacity and the quality of life. To our knowledge, only 1 study has investigated the effects of KT on pulmonary function and functional capacity of patients with COPD. Therefore, there is still a lack of high-quality evidence to prove the effectiveness of KT for COPD patients. In this study, our purpose was to investigate the effect of KT on respiratory function and muscle strength in the COPD patients who were in stable condition. It was hypothesized that thoracic KT could significantly change pulmonary function and functional capacity in patients with COPD. In our protocol, a total of 120 subjects will be recruited.

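### The between-arm Kruskal–Wallis test is valid but makes weak use of the baseline, and the within-arm Wilcoxon tests beside it should be labelled descriptive

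*Protocol article*

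**What the plan says.** Section 2.6 of the protocol article introduces two tests for what it calls nonparametric measures. Within arms, "differences between baseline and posttreatment scores for each group are computed by the Wilcoxon signed ranks test". Between arms, "The difference between each treatment group is performed by the Kruskal–Wallis test". Analysis of variance is named only for age, weight, height and body mass index. One threshold covers everything: "The level of statistical significance is set as" P < .05.

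The outcomes in section 2.5 are spirometry and maximum inspiratory and expiratory pressure. Section 2.3 mentions a baseline examination, and section 2.4 says that the researcher "completes posttreatment (15th day) evaluations for each patient". The signed ranks test needs a baseline score, so the plan already relies on having one.

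There are two arms, medical treatment with and without taping. On size, the Discussion says that "a total of 120 subjects will be recruited". No effect size, standard deviation or power is given.

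**The concern.** Two features of the stated analysis deserve attention.

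- **The between-arm test takes no covariate.** Each outcome is a continuous measure with a value before and after treatment. Adjusting for the baseline value usually sharpens the comparison. A rank test of day-15 scores leaves the baseline out, and a rank test of changes uses it less efficiently than adjustment does. The article does not say which score is ranked.
- **The within-arm tests have no stated role.** Section 2.2 admits patients with signs of an exacerbation, and section 2.3 gives medical treatment to both arms. Improvement over 15 days with no taping effect is therefore plausible. (The stated aim speaks of stable patients, in whom shared recovery would be smaller.) The hypothesis says that taping could significantly change function and makes no reference to the control arm, so a significant change in the taping arm could be taken to confirm it.

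At stake are power from data that will be collected anyway, and a clear statement of which P value answers the trial's question.

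**Working it through.** **Inputs from the article:** 120 patients in total, two arms, threshold 0.05, measurements at baseline and day 15.

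**Assumptions, because the article gives no figure:** 1:1 allocation (60 per arm; section 2.3 says only that "the randomization depends on random blocks of 10"), two-sided testing, a true effect of 0.4 SD of the outcome, normal data, and a correlation ρ between baseline and day 15, shown over a range. The figure of 120 cannot be reproduced, as it has no stated basis.

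**1. Precision of the between-arm comparison (normal theory).** With the outcome SD set to 1, the SD that governs the comparison is 1 for day-15 scores, √(2(1 − ρ)) for changes and √(1 − ρ²) for ANCOVA.

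- ρ = 0.5: 1, √1.0 = 1 and √0.75 = 0.866.
- ρ = 0.7: 1, √0.6 = 0.775 and √0.51 = 0.714.

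The effect detectable with 80% power is (1.960 + 0.842) × SD × √(2/60) = 0.511 × SD.

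| ρ | Detectable effect: day 15 / change / ANCOVA | Power at 0.4 SD: day 15 / change / ANCOVA |
|---|---|---|
| 0.3 | 0.511 / 0.605 / 0.488 | 59% / 46% / 63% |
| 0.5 | 0.511 / 0.511 / 0.443 | 59% / 59% / 72% |
| 0.7 | 0.511 / 0.396 / 0.365 | 59% / 81% / 87% |
| 0.9 | 0.511 / 0.229 / 0.223 | 59% / 99.8% / 99.9% |

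To match 120 patients analysed on day-15 scores, ANCOVA needs 120(1 − ρ²): 90 patients at ρ = 0.5 and 61 at 0.7. To match 120 analysed on changes it needs 120(1 − ρ²)/(2(1 − ρ)) = 60(1 + ρ): 90 at 0.5, 102 at 0.7 and 114 at 0.9.

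**2. The same comparison with the planned rank test, by simulation** (effect 0.4 SD, 60 per arm).

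| ρ | Kruskal–Wallis, day 15 | Kruskal–Wallis, change | ANCOVA | Rank ANCOVA |
|---|---|---|---|---|
| 0.5 | 57% | 57% | 72% | 69% |
| 0.7 | 55% | 78% | 85% | 82% |

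Repeat simulations agree within about 2 percentage points. With no taping effect, Kruskal–Wallis on either score and ANCOVA reject in 4.2% to 5.6% of trials, whatever the shared recovery.

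**3. The within-arm tests when taping does nothing.** Let both arms change by the same d, in SD of change. For normal data the signed ranks test in one arm has power p ≈ Φ(d × √60 × √(3/π) − 1.96), ignoring the far tail. The arms are independent, so the chance that only the taping arm is significant is p(1 − p), which cannot exceed 0.25.

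- d = 0.1: 0.1 × 7.746 × 0.977 = 0.76, p ≈ 0.12, p(1 − p) ≈ 10%.
- d = 0.25: 1.89, p ≈ 0.47, p(1 − p) ≈ 25%, the ceiling.
- d = 0.5: 3.78, p ≈ 0.97, p(1 − p) ≈ 3%; simulation gives 4%.

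The taping arm taken alone is significant in 46%, 62% and 96% of simulated null trials at d = 0.25, 0.3 and 0.5 (at ρ = 0.5, where the SD of change equals the SD of the outcome).

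**The case against.** The plan does contain a proper test of taping. With two arms, Kruskal–Wallis is equivalent to the Wilcoxon rank-sum test, is valid under randomization and holds its nominal error. This stands in full.

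A reader might infer that the plan wastes the baseline altogether. The text does not support that. Section 2.6 describes baseline-to-posttreatment differences first and the group comparison next, so ranking the changes is a reasonable reading, and then the baseline is used. On that reading the gain from ANCOVA is 7 points at ρ = 0.7, and it nearly vanishes at 0.9.

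A reader might also infer that the plan will count recovery in the taping arm as a taping effect. The article nowhere says so. It gives no order of precedence, and that is all that can be said. The 25% is a ceiling reached near one assumed value of recovery, not an expected error rate of this trial.

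Normal data favour ANCOVA. Rank ANCOVA is the fairer comparator: against Kruskal–Wallis on changes it gains 12 points at ρ = 0.5 and 4 at 0.7, the only two correlations at which it was examined. No skewed data were examined.

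Finally, this is a condensed article. Which score is ranked, and whether an effect estimate with a confidence interval will be reported, may be settled in a document not shown. Their absence here is not counted as an error.

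**Conclusion.** The point holds as a recommended improvement. The stated between-arm test is sound but less efficient than a baseline-adjusted comparison under either reading of section 2.6. At an assumed 0.4 SD effect the loss against ANCOVA is about 15 points of power at ρ = 0.5 on both readings. At ρ = 0.7 it is about 30 points if day-15 scores are ranked and 7 if changes are. The size depends on assumed values of ρ, effect, allocation and distribution, none of which the article supplies.

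The within-arm tests answer a different question from the trial's, and their role should be stated. The error rate of 4% to 25% applies only if their P values are used as evidence for taping. It would be wrong to conclude that the plan has an inflated type I error or that its efficacy test is invalid, so this does not rank as an error that must be fixed.

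**What to change.** In section 2.6, or in the analysis plan if there is one:

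- Make the test of taping for each outcome an ANCOVA of the day-15 value, with arm and the baseline value of the same measure as terms. Use rank ANCOVA if residuals are markedly non-normal.
- Report the adjusted between-arm difference with its 95% confidence interval, in the units of each measure.
- State that efficacy is judged on this comparison only.
- Report within-arm changes descriptively, without P values.

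The cost is a few sentences. The baseline scores are already required by the planned signed ranks test, no extra visit or measurement is needed, and SPSS, which the article names, runs ANCOVA. The wording should be settled before anyone sees outcome data by arm, so that the choice of score cannot follow the results.
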